# 3. METHODS

## 3.1. Study setting

Participants are enrolled from any of eight regions across the United States led by investigators at Rush University (Chicago, Illinois), Yale University (New Haven, Connecticut), the University of Washington (Seattle, Washington), Thomas Jefferson University (Philadelphia, Pennsylvania), the University of Texas Southwestern (Dallas, Texas), the University of Texas, Houston (Houston, Texas), the University of California, San Francisco (San Francisco, California) and the University of California, Los Angeles (Los Angeles County, California). The recruitment areas vary in terms of the population served to allow for ethnic and geographic diversity among study participants. As enrollment is through the internet and can be completed without assistance of research staff support, participants include those who have never been to the clinic or hospital for their symptoms and others who have been to the emergency department or hospitalized. Additionally, participants with any digital health portal can enroll in this study; participants’ health portals need not be those directly linked to the academic institutions listed above.

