## 3.5. Outcomes

Patient reported outcomes include self-reported disease-specific and generic health measures (Appendix A) [[21–23]](https://www.spiritprotocol.com/api/docx/https://paperpile.com/c/nKRweq/VLC3Q+9tpIp+1b0NF). Health care utilization and clinical events are extracted from the EMR data via Hugo as well as collected via patient self-report, ensuring uniform variable definitions across participating sites.

Self-report of symptoms suggestive of SARS-CoV-2 are assessed using questions derived from the Centers for Disease Control and Prevention (CDC) Person Under Investigation for SARS-CoV-2 survey (Appendix A) [[24]](https://www.spiritprotocol.com/api/docx/https://paperpile.com/c/nKRweq/QL4WH). This is not scored and has no predefined cutoff for the likelihood of COVID-19 illness.

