Cognition is assessed using the survey questions from the Patient-Reported Outcomes Measurement Information System (PROMIS^®^) Cognitive SF 8 [[32]](https://www.spiritprotocol.com/api/docx/https://paperpile.com/c/nKRweq/MUfAZ). Raw PROMIS^®^ Cognitive scores are re-scaled from raw scores of 8 (worst) to 40 (best) into standardized T-scores with a mean of 50 and standard deviation (SD) of 10. A higher score is interpreted as indicating greater cognition.

Health care process measures are assessed as ambulatory care and/or emergency department (ED) visits for symptoms related to COVID-19 illness as well as hospitalization (admitted to hospital overnight during study follow-up) as determined by data from the EMR.

Hospital-free and intensive care unit (ICU)-free survival are assessed as determined by data from the EMR [[33]](https://www.spiritprotocol.com/api/docx/https://paperpile.com/c/nKRweq/7mLIq). Hospital-free survival is survival without any hospitalizations and ICU-free survival is survival without time spent in the ICU.

Additional outcomes  assessed include post-infectious sequelae (e.g., dyspnea, cough) [[34–36]](https://www.spiritprotocol.com/api/docx/https://paperpile.com/c/nKRweq/crjeV+MWglS+v2y9g), post-traumatic stress disorder (PC-PTSD-5) [[37]](https://www.spiritprotocol.com/api/docx/https://paperpile.com/c/nKRweq/dFlhd), and exercise (exercise vital sign; 2 question survey to assess habitual physical activity) [[38–40]](https://www.spiritprotocol.com/api/docx/https://paperpile.com/c/nKRweq/E8xYP+3XcZq+NP9GE), using previously validated questionnaires .

Social determinants of health (e.g., housing, available social services, geographical location, and education) are assessed using a previously validated questionnaire [[41]](https://www.spiritprotocol.com/api/docx/https://paperpile.com/c/nKRweq/tBxfV).

Work and activity status are assessed using questions about returning to work, missed work and activity level (Appendix A).

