Patient-Centric Data Sharing: Participants connect their own health system portal account with the Hugo platform at enrollment (Figure 1). Hugo is a web-based platform used to longitudinally collect data for this study. The Hugo platform gives patients the ability to collect and maintain their personal health records in a centralized, cloud-based account. Participants will create a Hugo account and connect the health system portal accounts they choose to connect with the Hugo platform. This may include patient portals from healthcare systems, pharmacies, laboratories, and insurers. Individuals direct Hugo to share their health records with the research team according to the terms in the informed consent. This information is sent from Hugo to the research analytic core and stored in accordance with their institutional policies. The specific portal-related information available through Hugo in use for INSPIRE includes hospital and clinical patient portals yielding current data on medications, appointments and visits, test orders and results, clinical notes, problems, diagnoses, vital signs, demographics, and immunizations. After the study, participants can maintain their Hugo account or opt to delete their account and data.

Participants can connect their health system(s) portal accounts with Hugo at set up but may need assistance if they have technical issues or if they do not complete this initial step at enrollment. Once participants create an account in Hugo and link their portals, no additional actions are required to stream data into Hugo. Technical support from the enrolling site or clinical core is provided to resolve any difficulties setting up an account.

During the study, periodically Hugo downloads identifiable data outlined in the IRB protocol and consent form. Research sites have access to site-specific dashboards to track enrollment, identify which data sources are connected, and to monitor survey responses. Deidentified, individual-level data are sent from Hugo to the analytic team periodically for quality assurance and analysis.

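### Hospitalization, hospital-free and ICU-free survival are fixed from the EMR alone although the same section names self-report as a second source, so events in portals a participant did not link are silently counted as no event

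*Protocol*

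**What the plan says.** Protocol section 3.5 gives two accounts of where these outcomes come from.

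- The general statement names two sources: "Health care utilization and clinical events are extracted from the EMR data via Hugo as well as collected via patient self-report". It presents this as giving the same variable definitions at every site.
- The specific definitions later in the section name one. The health care process measures end with "hospitalization (admitted to hospital overnight during study follow-up) as determined by data from the EMR", and for the composite outcomes "Hospital-free and intensive care unit (ICU)-free survival are assessed as determined by data from the EMR". The event is broad: "Hospital-free survival is survival without any hospitalizations".

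Section 3.6.1 describes the EMR feed. Participants create an account and "connect the health system portal accounts they choose to connect with the Hugo platform". They "may need assistance if they have technical issues or if they do not complete this initial step at enrollment". Section 3.1 adds that "health portals need not be those directly linked to the academic institutions listed above". The same section 3.6.1 sends surveys every 3 months for 18 months, and these ask about health care use.

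Section 3.9.1 lists these outcomes for comparison by age and SARS-CoV-2 status. For missing data it says that multiple imputation will be considered, with a sensitivity analysis limited to people whose outcome is not missing.

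**The concern.** The protocol does not say which source governs or how disagreements are settled. Two analysts could each follow section 3.5 and reach different event counts.

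If the specific definitions govern, the outcome covers any admission, but the feed sees only linked systems. A participant who links one system and is admitted in another has a record with no admission in it. That record looks complete, so the participant counts as hospital-free.

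At stake are the absolute rates of hospitalization, ICU stay and visits, which are descriptive aims of the study, and the risk differences built on them. If linkage also differs between test-positive and test-negative participants, the risk ratio is distorted as well. Meanwhile self-reported health care use, already collected, has no stated part in the outcome.

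**Working it through.** **1. The text, side by side**

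| Item | Source named | Section |
|---|---|---|
| Utilization and clinical events, general | EMR and self-report | 3.5 |
| Hospitalization | EMR | 3.5 |
| Ambulatory and emergency visits | EMR on the natural reading (same sentence as hospitalization) | 3.5 |
| Hospital-free and ICU-free survival | EMR | 3.5 |
| Content of the EMR feed | portals the participant chooses to link | 3.6.1 |

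**2. What happens to an event outside the linked portals**

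- Some portals linked, event elsewhere: the feed holds data but not the event. The outcome reads as no event, with nothing missing to impute. The analysis of non-missing outcomes keeps the participant as event-free.
- No portal linked: there is no feed. The outcome can be treated as missing under section 3.9.1, although the protocol does not say that it will be.

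The silent under-count is therefore firm for the first group and not established for the second.

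**3. The plan's own power figure, as a reference point**

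Inputs from sections 3.8: n₁ = 3,600 positive, n₀ = 1,200 negative, p₀ = 0.025, absolute difference 0.025 so p₁ = 0.05, alpha 0.05 (taken as two-sided).

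Power = Φ[(|p₁ − p₀| − 1.96·s₀) / s₁], where s₀ is the standard error under the pooled rate and s₁ under the separate rates.

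- Pooled rate = (1,200 × 0.025 + 3,600 × 0.05) / 4,800 = 0.04375
- s₀ = √[0.04375 × 0.95625 × (1/1,200 + 1/3,600)] = 0.006818
- s₁ = √[0.025 × 0.975/1,200 + 0.05 × 0.95/3,600] = 0.005789
- Power = Φ[(0.025 − 0.013363) / 0.005789] = Φ(2.01) = 97.8%, as stated.

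**4. Illustration: same capture in both groups**

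The documents give no capture fraction c, so the values below are assumptions. Observed rate = c × true rate, with no false events.

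| c | Positive vs negative | Difference (points) | Risk ratio | Power |
|---|---|---|---|---|
| 100% | 5.0% vs 2.5% | 2.5 | 2.0 | 97.8% |
| 90% | 4.5% vs 2.25% | 2.25 | 2.0 | 96.3% |
| 70% | 3.5% vs 1.75% | 1.75 | 2.0 | 90.0% |
| 50% | 2.5% vs 1.25% | 1.25 | 2.0 | 76.2% |

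**5. Illustration: capture differs by group, no true difference**

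The apparent risk ratio is c₁/c₀ (positive over negative). Two-sided rejection at true rates of 2.5%, 5% and 10%, against a nominal 5%:

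| c₁ / c₀ | Apparent risk ratio | Rejection |
|---|---|---|
| 85% / 80% | 1.06 | 5.4%, 6.3%, 8.1% |
| 90% / 75% | 1.20 | about 11%, 19%, 35% |
| 75% / 90% | 0.83 | about 14%, 22%, 39% |

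The result runs from negligible to serious, in either direction, depending on an unknown gap.

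**The case against.** The two statements can be read together: the first says what is collected, the later ones say which source decides. Using the record as arbiter fits the aim in section 2.1 of objective outcomes, and source precedence is often left to an analysis plan. This is a fair reading, and it removes the contradiction. It does not remove the under-count, because it confirms that the EMR alone decides, and a partial feed then determines the outcome.

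Section 3.6.1 also has participants connect a portal at enrollment, offers technical support, and gives sites dashboards showing which sources are connected. These steps reduce non-linkage but do not make linkage complete.

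Three stronger readings are tempting, and the documents do not support them.

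- That every participant with no linked portal is scored event-free. No section says so, and section 3.9.1 leaves room to treat them as missing.
- That the comparison by test status is biased. Recruitment routes in section 3.3 vary by site and are not tied to test result. Nothing shows that linkage differs by group.
- That the stated 97.8% power is lost. Section 3.8 calls the calculation outcome-agnostic and names ME/CFS as a specific comparison. ME/CFS is assessed by a survey screener, which portal linkage does not affect.

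Self-report has its own faults: recall error, survey non-response, possible differences in reporting among people who know their test result, and no capture of deaths. These argue for showing both versions, not for the EMR alone.

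**Conclusion.** The point holds in a limited form. The specific definitions in section 3.5 rest on the EMR alone, the general statement does not, and the feed is incomplete by design. For partly linked participants an event in an unlinked system becomes a non-event that the missing-data methods cannot detect, so rates are biased downward. Equal under-capture shrinks risk differences but leaves the risk ratio alone. Unequal capture would bias the ratio either way, but whether it occurs is unknown. All capture fractions are assumptions, and the 97.8% serves only as a yardstick. This should be corrected before the utilization outcomes are analyzed. It does not touch the survey-based outcomes.

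**What to change.** - Bring the specific definitions in section 3.5 into line with the general one: a hospitalization, ICU stay or visit counts if it is in the EMR or self-reported in a 3-monthly survey. Take deaths from whatever source records them.
- Report an EMR-only version as a sensitivity analysis, with participants who have no linked portal treated as missing rather than event-free. Restricting it to people with at least one linked portal would not cure partial linkage, so it should not be the main analysis.
- Censor follow-up at the last portal refresh or survey.
- Report linkage completeness by test status, so that readers can judge whether unequal capture is a live issue.

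The cost is a change of wording and a linkage variable. The surveys already collect health care use and the dashboards already show connected sources, so no new data collection is needed. The downside is that some self-reported events will be less certain and open to recall error and survey non-response. The EMR-only sensitivity analysis makes that visible. An event that is neither linked nor reported will still be missed.

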## 3.2. Eligibility criteria

This study includes adult patients who are under clinical investigation for possible SARS-CoV-2 infection and who meet inclusion criteria outlined in Table 1. We include individuals with symptomatic presentation to determine comparative frequency of outcomes amongst symptomatic individuals with and without SARS-CoV-2 infection: symptomatic individuals presenting with covid-like illness who test negative will act as controls for symptomatic individuals who have positive tests for SARS-CoV-2. Asymptomatic individuals are not eligible, given the anticipated lower rates of outcomes among asymptomatic individuals who test positive for SARS-CoV-2, and the significant heterogeneity in reasons for testing in asymptomatic individuals, such as screening for social, educational, occupational reasons and prior to routine clinical procedures. Individuals who self-report symptoms suggestive of acute SARS-CoV-2 infection, and are tested for SARS-CoV-2 within the last 42 days, are eligible to participate. From study initiation through the summer of 2021, symptoms of acute SARS-CoV-2 was defined using the COVID-19 clinical criteria case definition (Table 2) [[18]](https://paperpile.com/c/nKRweq/MqHQg); beginning summer of 2021, in order to capture less symptomatic individuals, the inclusion criteria were revised to require only one symptom among those listed in Table 2. Individuals for whom a SARS-CoV-2 test result cannot be confirmed are not eligible to participate in the study. Efforts are made to recruit participants from across the spectrum of COVID-19 illness severity, including individuals from outpatient (e.g., drive through testing with self-reported symptoms) to inpatient settings, and those cared for in intensive care units. We seek to enroll using a 3:1 case/control ratio to oversample those who are positive for SARS-CoV-2 on testing, while still ensuring an adequate control cohort for comparison.

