## 3.9. Statistical methods

### 3.9.1. Outcomes

Statistical analyses will describe disease course and outcomes, including the characterization of specific symptoms and duration of symptoms, health care utilization (emergency department, hospitalization, post-acute care) with clinical (morbidity/mortality) and patient-reported health status outcomes as well as recovery (early and late disease sequelae). Baseline and demographic characteristics will be summarized by descriptive summaries (e.g., means and standard deviations for continuous variables such as age and percentages for categorical variables such as gender, medians, and quartiles for skewed data). Analyses will:

- Compare health status at baseline and follow-up between persons in the same age group who test SARS-CoV-2 positive and negative at initial test.
- Characterize health care utilization (ambulatory and ED visits, hospitalizations, post-acute care, telehealth visits) among SARS-CoV-2 positive participants by age and compare these to SARS-CoV-2 negative participants.
- Characterize and compare health outcomes by age and SARS-CoV-2 status: emergency or ambulatory care, admission to hospital); ICU-free survival;^16^ hospital-free survival; and subsequent patient-reported health status (cognition; physical health; mental health; and return to work).

We will use statistical modeling to estimate the association between key covariates and outcomes, including evaluating interactions by age. We plan to use survival analysis techniques to analyze time to outcome events, logistic regression for binary outcomes (e.g., hospitalization versus no hospitalization), Poisson or Cox regression for count data (e.g., number of hospitalizations over time), and linear regression models for continuous outcomes (e.g., PROMIS-29). Multiple imputation will be considered to handle missing covariate and outcome data in these analyses [[43]](https://www.spiritprotocol.com/api/docx/https://paperpile.com/c/nKRweq/3dpny). Chained equations will be used to impute each variable with missing data. Sensitivity analyses will be conducted using missing categories for covariates and including only people with non-missing outcome information.

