We will use statistical analyses to address the risk of ME/CFS and other health conditions in those with versus without SARS-CoV-2 infection as risk difference or risk ratios or odds ratios, as appropriate. We will also adjust for additional patient-level factors of interest, including age, sex, race/ethnicity, income, and presence of specific underlying conditions such as hypertension and diabetes. We anticipate that as more is learned about the clinical courses of persons with symptomatic SARS-CoV-2 infection, additional covariates of interest available from electronic record data will be assessed for their association with adverse outcomes.

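### Hospitalization, hospital-free and ICU-free survival count admissions of every kind, so deliveries and scheduled procedures dilute the ratio comparison by SARS-CoV-2 status; an unplanned, non-obstetric version should be prespecified alongside

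*Protocol*

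**What the plan says.** Protocol section 3.5 (Outcomes) defines the three measures without regard to cause or planning:

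- Hospitalization: "hospitalization (admitted to hospital overnight during study follow-up) as determined by data from the EMR".
- Hospital-free and ICU-free survival: "Hospital-free survival is survival without any hospitalizations and ICU-free survival is survival without time spent in the ICU".

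The sentence that defines hospitalization does restrict the neighbouring measure by cause. It counts "ambulatory care and/or emergency department (ED) visits for symptoms related to COVID-19 illness".

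Table 1 in section 3.2 excludes neither pregnancy nor people awaiting a scheduled procedure. Participants are adults from age 18, followed for 18 months (section 3.6.1).

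Section 3.9.1 then uses these outcomes for the comparison of interest: "Characterize and compare health outcomes by age and SARS-CoV-2 status". The list that follows includes hospital admission, ICU-free survival and hospital-free survival. Logistic regression is named for hospitalization and survival methods for time to event. Adjustment is planned for patient-level factors, "including age, sex, race/ethnicity, income, and presence of specific underlying conditions such as hypertension and diabetes". For ME/CFS and other health conditions, risk differences, risk ratios and odds ratios are all allowed.

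**The concern.** The stated objective (section 2.2) is to understand the sequelae of symptomatic infection. As defined, a delivery, a booked operation or a planned ICU stay after surgery counts the same as an admission for a late complication. An ED visit for an unrelated problem is not counted under section 3.5, but the overnight admission that follows it is. The protocol does not say whether this difference is intended.

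Events that have nothing to do with infection raise the observed risk in both groups. They add noise, and they shrink the measures that logistic and survival models usually report. A weak or null result for hospitalization could then mean that infection has little effect on admissions, or only that the effect is buried under unrelated ones. The all-cause analysis alone cannot separate the two.

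**Working it through.** **Inputs from the protocol.** 3,600 test-positive and 1,200 test-negative participants and alpha 0.05 (section 3.8). Baseline rate 2.5% and absolute difference 2.5 points, so 5.0% versus 2.5%, with stated power 97.8% (section 3.8). The scenario is outcome-agnostic; using it for illness-related admissions is an assumption made here.

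**Input not in the protocol.** The 18-month risk *b* of an unrelated admission. It is varied over 2% to 10%, taken as equal in both groups and independent of illness-related admission.

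**Step 1: reproduce the stated power.** Two-sided test, pooled variance under the null, no continuity correction:

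- Pooled rate = (1,200 × 0.025 + 3,600 × 0.05) / 4,800 = 0.04375
- SE under the null = √[0.04375 × 0.95625 × (1/1,200 + 1/3,600)] = 0.00682
- SE under the alternative = √[0.025 × 0.975/1,200 + 0.05 × 0.95/3,600] = 0.00579
- z = (0.025 − 1.96 × 0.00682) / 0.00579 = 2.01, so power = 97.8%, as stated.

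**Step 2: add unrelated admissions.** With illness-related risk *p*, the observed risk is q = 1 − (1 − p)(1 − b). For b = 5%:

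- Test-negative: 1 − 0.975 × 0.95 = 7.375%
- Test-positive: 1 − 0.95 × 0.95 = 9.75%
- Risk ratio = 9.75 / 7.375 = 1.32; risk difference = 2.375 points
- SE under the null 0.00961, under the alternative 0.00902; z = (0.02375 − 1.96 × 0.00961) / 0.00902 = 0.54, so power = 71%.

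**Step 3: the range.** The hazard ratio is ln(1 − q₁)/ln(1 − q₀), with q₁ for test-positives and q₀ for test-negatives, assuming proportional hazards.

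| b, both groups | Observed risk, positive vs negative | Risk difference (points) | Risk ratio | Odds ratio | Hazard ratio | Power |
|---|---|---|---|---|---|---|
| 0% | 5.00% vs 2.50% | 2.50 | 2.00 | 2.05 | 2.03 | 97.8% |
| 2% | 6.90% vs 4.45% | 2.45 | 1.55 | 1.59 | 1.57 | 88% |
| 5% | 9.75% vs 7.38% | 2.38 | 1.32 | 1.36 | 1.34 | 71% |
| 8% | 12.60% vs 10.30% | 2.30 | 1.22 | 1.26 | 1.24 | 57% |
| 10% | 14.50% vs 12.25% | 2.25 | 1.18 | 1.22 | 1.20 | 50% |

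**Step 4: can the direction change?** With equal *b*, the risk difference is (1 − b)(p₁ − p₀), where p₁ and p₀ are the illness-related risks in positives and negatives. It shrinks but keeps its sign. With unequal rates, the observed risks are equal when (1 − p₀)(1 − b₀) = (1 − p₁)(1 − b₁). At 5.0% versus 2.5%:

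- b₁ = 2%: b₀ = 1 − 0.95 × 0.98/0.975 = 4.5%
- b₁ = 5%: b₀ = 1 − 0.95 × 0.95/0.975 = 7.4%

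A reversal therefore needs about 2.5 points more unrelated admissions among test-negatives.

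**The case against.** All-cause admission is clear, objective and applied identically to both groups. It needs no judgement about attribution, and it fits the call in section 2.1 for objective outcomes that go beyond symptoms. Whether scheduled or obstetric care changes after infection is also something this cohort could examine. That stands, and it is the reason to keep the all-cause measures.

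The difference from ED visits is not a contradiction in itself. Symptom-driven visits and overnight stays are different measures, and section 3.9.1 lists visits and admissions together without repeating the cause restriction. That also stands; what is open is whether the difference is intended.

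The sample-size scenario is outcome-agnostic and hospitalization is not named as a powered outcome. The power losses are therefore illustrations. It is also true that the risk difference hardly moves, but choosing it does not restore power, because the added events raise the variance.

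A reader might go further and infer that the definition could reverse the contrast: people tested before a procedure, with a minor symptom and a negative result, would become controls who are then admitted. The documents do not support this. Section 3.2 mentions such testing ("such as screening for social, educational, occupational reasons and prior to routine clinical procedures") among its reasons for making asymptomatic people ineligible. Participants must report symptoms, and staff who screen the EMR look at the reason for testing (section 3.3). The single-symptom rule from summer 2021 leaves some room for this route, but nothing shows that it is common. A procedure postponed after a positive test still counts if it takes place within the 18 months. Adjustment for age, sex and underlying conditions is planned, although it does not directly capture a booked procedure or a current pregnancy.

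Finally, coding of admission types is often left to a statistical analysis plan, and none is shown here. The point therefore rests on the definitions that the protocol does fix, not on the absence of coding detail.

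**Conclusion.** The concern holds as a design choice that should be supplemented. It is not an error or a contradiction. As written, deliveries and scheduled overnight procedures are hospitalization events and failures of hospital-free survival, and any ICU time is a failure of ICU-free survival.

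If unrelated admissions are equally frequent in both groups, a true doubling of illness-related admissions appears as a risk ratio of 1.55, 1.32 or 1.22 at assumed unrelated rates of 2%, 5% and 8%. Power is then 88%, 71% or 57% instead of 97.8%, and the risk difference falls only from 2.50 to between 2.45 and 2.30 points. These figures rest on a borrowed event rate, on assumed rates of unrelated admission and on independence of the two kinds of admission.

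A reversed direction is not part of the conclusion. It would require an excess of about 2.5 points among test-negatives, which the documents neither state nor imply.

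**What to change.** In section 3.5, keep the all-cause definitions of hospitalization, hospital-free survival and ICU-free survival, and state that they are intended to be all-cause. Beside each, prespecify a version restricted to unplanned, non-obstetric admissions; for ICU-free survival, count only ICU time within such admissions.

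Classify admissions by a fixed rule on EMR encounter and diagnosis data, applied identically to all participants and without using SARS-CoV-2 status. Section 3.6.1 shows that visits and diagnoses already reach the study through the connected portals, so no new data collection is needed. A rule based on codes is preferable to reading clinical notes, because the same data stream carries test results and a reader could not easily be kept unaware of them.

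In section 3.9.1, report both versions in the comparison by SARS-CoV-2 status.

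The cost is a modest amount of coding work and one further set of analyses. Some admissions will be misclassified as planned or unplanned; reporting the all-cause version alongside makes the effect of that visible.
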